A new opportunity is the use of virtual technologies to expand the reach of such trials. While access to high-speed internet among rural populations is substantially lower than urban populations (45.6% vs. 98.6%), government initiatives to expand rural broadband connection are on track to reach 95% of the Canadian population by 2026 [33, 34]. The COVID-19 pandemic has also positively contributed to the virtual delivery of lifestyle interventions, expanding the geographical reach of interventions in research and in practice, while technology use among older adults has accelerated as 75% of older adults now feel confident using current technology [35]. Furthermore, virtual or online programs limit the barriers to participation in in-person programs, for example, the need for transportation and navigating cities and facilities that are not always accessible [36–38]. Overall, this suggests a sizable audience of older adults who could and may be inclined to access virtual group interventions.

In the long-term, the research team’s aim is to conduct a fully powered, virtual, factorial RCT, which will require 404 participants over 3.5 years. The planned future primary outcome will be executive function. Although, before embarking on such a large, expensive trial, it is important to first determine that such a trial will be feasible. While several studies have demonstrated the feasibility of virtual exercise and education interventions [39–42], including those for individuals with cognitive impairment [36, 43, 44], there is no existing literature to support the feasibility of a 6-month, virtual RCT with follow-up at 12 months and compliance to an active control group that is time/frequency matched to intervention groups.

Overall, the ultimate aim of this study is to determine the feasibility of an entirely virtual factorial RCT; a 6-month virtual exercise and nutrition trial among older adults with subjective cognitive decline. This factorial RCT will examine the independent and combined effects of aerobic and resistance exercise versus stretching control, and healthy diet counseling versus brain health education control on executive function among people with SCD.

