### Recruitment process and strategy

Recruitment of participants began in July 2023 and is expected to be completed in December 2024. The target is to recruit 140 participants across 5 waves, using a variety of recruitment strategies to increase the likelihood of reaching diverse older adults: directed mailings, social media, websites, radio/newspaper advertisements, research and community organization email lists, partner websites and centers, and outreach to physician/seniors’ groups. Participants will also be recruited from targeted research pools and partners email lists including the investigators’ research institutes, the Canadian Consortium for Neurodegeneration in Aging (CCNA), and other project partners.

Potential participants will be contacted by telephone by a member of the research team who will go through the recruitment script to describe the study and screen for eligibility. During this call, a brief assessment for SCD will be conducted. Eligible participants will be sent an electronic version of the letter of information and consent form and will schedule their second screening visit to rule out objective cognitive impairment. All eligible participants will then complete virtual assessments 1 and 2 within 6 weeks of their program start date. Once the assessments are completed, participants will be randomized into one of the four study arms. See Table 1 for an outline of the assessments and timeline.

**Table 1 Tab1:** Schedule of study assessments

Timepoint	Study timeline			
	Enrollment	Baseline	Post-Int	Follow-up
	− t_1_	t_1_	t_2_	6 months after t_2_ assessment, t_3_
Screening and enrollment				
Screening visit #1	X			
Informed content	X			
Screening visit #2	X			
Virtual assessment 1				
Sociodemographic information		X		
Language proficiency and acquisition		X		
Medical and mental health history		X	X	X
Current medications		X	X	X
Technology proficiency survey		X		
PASE		X	X	X
EPSA		X	X	X
Waist circumference		X	X	X
5 × sit to stand test		X	X	X
SF-36		X	X	X
CES-D		X	X	X
GAI		X	X	X
Virtual assessment 2				
CBS Double Trouble Stroop Test		X	X	X
CBS Monkey Ladder		X	X	X
CBS Feature Match		X	X	X
CBS Paired Associates task		X	X	X
RAVLT		X	X	X

*PASE *Physical Activity Scale for the Elderly, *EPSA *Eating Pattern Self-Assessment, *SF-36 *Short-Form 36, *CES-D *Center for Epidemiological Studies Depression Scale, *GAI *General Anxiety Inventory, *CBS *Cambridge Brain Sciences, *RAVLT *Rey Auditory Verbal Learning Test

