### Randomization and blinding procedure

Participants will be randomly assigned (1:1:1:1) after baseline assessments, stratified by gender (man/woman, and if sufficient in number, non-binary/self-described) and balanced within blocks of variable size (4 or 8) to avoid predictable participant allocation. Eligible partnered couples will be randomized together. The randomization sequence will be computer-generated and maintained by an assistant not affiliated with the study. Once baseline assessments are complete, the research coordinator will provide the participant ID to the randomization assistant who will inform the coordinator of the group allocation, which will be communicated to the participant. Participants will start the trial in waves of 24 to 32 (6 to 9 people per group; every 3 months) to ensure sufficient sample size for group dynamics and social support.

Assessors will be blinded to group assignment and participants will be asked not to mention their group assignment to assessors. Standardized instructions will be provided for assessments. To keep participants blinded from the study hypotheses and to minimize group effect expectations, the content of the intervention and the wording of recruitment documents and consent forms will not convey the differences between EX and STRETCH. Participants will be told that the groups will differ in the type of brain health education that is provided (DIET versus ED).

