### Primary outcome measures

#### Feasibility: recruitment, adherence, retention

i)Recruitment.

A research coordinator will be responsible for logging recruitment activities as participants contact the study email or phone number. The research coordinator will document the following information of each participant: name, phone number, email, date of first contact, how they heard of the study, and whether they passed telephone screening. For participants that pass initial screening, they will be scheduled to meet with an assessor for a second screening and to provide consent. Upon completing the second screening session, the research coordinator will document whether they passed or failed screening. Recruitment feasibility will be determined by the average number of participants recruited per month (target: ≥ 9 participants per month).

ii)Adherence.

Instructors will keep a detailed attendance record for each component of each session (EX/STRETCH and DIET/ED). The target is ≥ 75% of EX and ≥ 75% of DIET sessions completed [66]. Adherence will be measured through subjective participation scores that are completed by the instructor and volunteer of each session, as well as by self-reported RPE ratings provided each session by participants in the EX groups. For each EX/STRETCH and DIET/ED component, participants will be confidentially scored on a scale from 1 to 3. A score of 3 indicates that the participant actively followed along with all exercises/stretches or DIET/ED content and participated in exercises/stretches or listened or contributed greater than 80% of the session. A score of 2 indicates that a participant engaged/contributed to 50–80% of the session and a 1 indicates that a participant engaged in less than 50% of the session. Self-reported attendance records for the independent sessions will also be collected, noting RPE rating (for EX groups), and any symptoms experienced during EX and STRETCH. For diet quality specifically, adherence will be measured through adherence to the Brain Health Food Guide recommendations and will be assessed using the Eating Pattern Self-Assessment (EPSA) [54].

iii)Retention.

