### Sample size

A recent meta-analysis of exercise on cognition found Cohen’s *d* effect sizes between 0.27 and 0.36, dependent on combinations of exercise mode, frequency, duration, and outcome [16]. Effect sizes for diet interventions are highly variable depending on the intensity of the intervention. The most similar published diet intervention was in a factorial RCT of exercise and diet (without a goal-setting component) that found an effect size of 0.32 for exercise and 0.30 for diet [82]. The intensity of the current study intervention is higher than in this prior study, and it is expected that the goal-setting will increase adherence. However, virtual delivery may weaken adherence. As a result, an effect size of 0.30 was chosen for sample size estimates for the full-scale trial.

For the full-scale trial, it is estimated that 88 participants are needed per intervention arm (total of 364 participants) to detect EX (*d* = 0.3) and DIET (*d* = 0.3) effects with an alpha level of 5% and 80% power. With 10% dropout, 404 participants are needed for a full-scale trial over 3.5 years. As a result, for this feasibility trial, 140 participants will be recruited over 1.25 years to test the feasibility of the rate of recruitment that would be required for the full trial. Interim analysis of feasibility will be performed after the first three waves complete the 6-month assessment.

This sample size should also be appropriate for measuring feasibility outcomes. To confirm the sample size was sufficient, we considered a study adherence as a dichotomous outcome with a binomial distribution, where each participant will either complete the 6-month assessment (1) or not (0). With a sample size of 140, anticipated adherence of 80% can be estimated to within a 95% confidence interval from 72% to 86%.

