### Analysis

Analysis of primary objectives related to feasibility outcomes will be descriptive. “Success” will be based on predetermined criteria outlined in “Objectives and hypothesis” which included: (1) Recruitment: ≥ 9 participants/month over 1.25 years; (2) Adherence: (a) ≥ 75% of Aerobic and Resistance Exercise (EX) sessions and ≥ 75% of Diet Counseling (DIET) sessions are completed; (b) improvement in diet quality at 6 months compared to baseline; (3) Retention: ≥ 80% of randomized participants complete the 6-month assessment of executive function. Overall, “success” will indicate that the protocol is adequately robust to proceed to a large RCT with small or no adaptations, and failure to meet these targets indicating a need for substantial change before proceeding. Preliminary analyses of feasibility outcomes will be conducted at the end of year 2 by an independent statistician when the first three waves complete their 6-month assessment. If the data support feasibility, the research team will apply for funding to roll directly into the definitive trial.

Full analyses will be conducted once all participants have completed their 12-month follow-up assessments. Analyses will explore whether feasibility outcomes vary by gender as research suggests that exercise and diet preferences vary by gender [45, 84]. Feasibility outcomes will be described among women and men, and among non-binary and other gender groups if possible. Analyses will also explore whether other demographics, geographical location, or technology access predict adherence. Characteristics of the participants who withdraw and reasons for withdrawal will be analyzed and intent-to-treat analyses will be used. Individuals who withdraw from the study will be invited to take part in post-intervention and 6-month post-intervention assessments and a sensitivity analysis will be completed. In addition, effect sizes for EX and DIET will be determined for the future, full-scale trial by gender. An analysis of effect sizes will be conducted from both intention-to-treat and per protocol analyses (to understand potential effectiveness in relation to adherence).

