### Trial status

Participant recruitment began in July 2023. The first session of the intervention began in October 2023 and the last session of the intervention is scheduled to finish in June 2025.

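### The recruitment pass mark of 9 per month is below the rate the full trial needs (9.3 to 9.6), and its 15-month window conflicts with the 17 to 18 month recruitment calendar

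*Protocol article*

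**What the plan says.** The Objectives and Analysis sections set the recruitment criterion at no fewer than "9 participants/month over 1.25 years". The outcome definition repeats the monthly target but gives no window or start date: "Recruitment feasibility will be determined by the average number of participants recruited per month".

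The Sample size section gives the purpose: "140 participants will be recruited over 1.25 years to test the feasibility of the rate of recruitment that would be required for the full trial". The full trial is described there as "With 10% dropout, 404 participants are needed for a full-scale trial over 3.5 years", and in the Background as a "factorial RCT, which will require 404 participants over 3.5 years".

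The calendar is given elsewhere. Under Recruitment process and strategy: "Recruitment of participants began in July 2023 and is expected to be completed in December 2024", with 140 people planned across five waves. Under Randomization and blinding procedure: "Participants will start the trial in waves of 24 to 32 (6 to 9 people per group; every 3 months". Under Trial status, the first session was in October 2023 and "the last session of the intervention is scheduled to finish in June 2025".

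Under Analysis, meeting the criteria means going on to the large trial with little or no change, and missing them means substantial change first. A supportive preliminary analysis leads to a funding application for the definitive trial.

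**The concern.** Recruitment is one of three criteria that decide whether the definitive trial goes ahead. Two things look wrong with how it is fixed.

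First, the threshold is lower than the rate it is meant to demonstrate, so a pass would not show that the full trial can be filled in 3.5 years.

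Second, the criterion refers to a 15-month period, but the stated recruitment dates span 17 to 18 months. A trial that runs exactly to its published calendar and enrols everyone it planned to enrol would fall short of its own mark. Because the outcome definition gives no start or end date, the reported rate depends on a choice the article does not make.

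**Working it through.** **Inputs.** Pass mark 9 per month over 1.25 years = 15 months (Objectives, Analysis). Pilot target 140 in five waves, July 2023 to December 2024 (Recruitment process and strategy). Waves every 3 months (Randomization and blinding procedure). First session October 2023, last June 2025 (Trial status). Full trial: 88 per arm, stated total 364, 10% dropout, 404 over 3.5 years = 42 months, d = 0.3, alpha 5%, power 80% (Sample size).

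**1. Reproduce the plan's figure.** 364/(1 − 0.10) = 404.4, so 404 follows from 364. However, 4 × 88 = 352, not 364. A two-sided comparison of means at d = 0.3 with 80% power needs 350 to 352 in total, which supports 88 per arm. From 352 the inflated total is 352/0.9 = 391.1, or 392. Both bases are carried below.

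**2. Rate the full trial needs.**
- 404/42 = 9.62 per month.
- 392/42 = 9.33 per month.
- Pilot plan: 140/15 = 9.33 per month.

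All exceed 9.

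**3. What a bare pass delivers.**
- Pilot: 9 × 15 = 135, which is 5 short of 140.
- Full trial: 9 × 42 = 378, which is 26 short of 404.
- After 10% dropout: 378 × 0.9 = 340 analysed.
- Power = Φ(0.3 × √(340/4) − 1.96) = Φ(0.806) = 79%. The same formula gives 80.4% at 352 and 81.6% at 364.
- Time to 404 at 9 per month: 404/9 = 44.9 months.

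**4. Rate implied by the calendar.** July 2023 to December 2024 is 18 calendar months counted inclusively, or 17 from month to month.
- 140/18 = 7.78 per month; 140/17 = 8.24 per month.
- Holding 9 per month over those spans would need 9 × 18 = 162 or 9 × 17 = 153 people, both more than the 140 planned.

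**5. Which dates agree with each other.**
- Five waves × 3 months = 15 months. 140/5 = 28 per wave, and 28/3 = 9.33 per month. So the wave plan, the 140 and the 1.25 years are consistent.
- Fifteen months from July 2023 ends in September 2024. Five waves starting in October 2023 and every 3 months after that put the last start in October 2024 and, with a 6-month programme, the finish in April 2025.
- A June 2025 finish implies a last start around December 2024, which fits the December 2024 end of recruitment. Four gaps between October 2023 and December 2024 are 14/4 = 3.5 months each, and 28/3.5 = 8.0 per month.

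The article therefore carries two schedules, one ending about September/October 2024 and one about December 2024. Only the first is compatible with 9 per month for 140 people.

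**The case against.** The best defence of the threshold is that 9 is simply 9.33 rounded down, and that the gap is trivial. That largely stands. The cost is about one point of power against the planned 80%, and a count of 140 in 15 months has a Poisson 95% range of (140 ± 1.96 × √140)/15, or roughly 7.8 to 10.9 per month, which cannot separate 9 from 9.33 or 9.62. The analysis is descriptive, so the observed rate can be set beside the required one in any case. What remains is that the stated threshold does not match its stated purpose.

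On the window, October 2023 to December 2024 is 15 months counted inclusively. But the article dates the opening of recruitment to July 2023 and nowhere defines the window from the first session. Counting from October would drop about three months of open recruitment while keeping the people recruited in them.

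A reader might infer several stronger points that the documents do not support:

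- *The same 140 people pass or fail according to the divisor.* The Objectives and Analysis text fixes 15 months, so people enrolled in months 16 to 18 cannot properly be divided by 15. The defect is that this window and the calendar disagree, and that the outcome definition omits the window.
- *The planned waves themselves fail the mark.* That holds only at the bottom of the 24 to 32 range. The planned average of 28 gives 9.33.
- *The 140 might not be randomised people.* The article describes them as receiving the interventions and starting in waves, and uses them as the base for 6-month completion. At most the monthly count needs the word randomised.
- *The full trial would end up badly underpowered at the calendar rate.* A rate of 7.8 fails the criterion, and the plan then calls for substantial change. The period also includes a first month under a narrower screen that was dropped because recruitment was low.

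**Conclusion.** The point holds. The pass mark is 4% below the pilot's own planned rate (9 against 9.33) and 6% below the full-trial rate (9 against 9.62). Taken alone this is a modest mismatch: 378 rather than 404 after 42 months, about 79% power, or about three extra months to reach 404. The calendar conflict is the weightier part. On the published dates, full recruitment on schedule gives 7.8 to 8.2 per month and misses the criterion.

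Assumptions:
- Alpha is taken as two-sided; the article does not say.
- All 42 months are treated as recruitment time. If the 3.5 years also include 6 or 12 months of follow-up, the need rises to 404/36 = 11.2 or 404/30 = 13.5 per month, so 9.62 is a lower bound for 404.
- Pilot participants are not counted towards the 404. The article speaks of rolling into the definitive trial but does not say they are carried over.
- The range 7.8 to 8.2 reflects 18 or 17 months.

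It does not follow that the mark must be raised to 9.6. That figure rests on 364, which is not 4 × 88, and raising a pre-determined threshold with recruitment under way is harder to defend than keeping it and correcting what it is said to show.

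**What to change.** 1. Define the recruitment rate once, in the outcome definition, and refer to it elsewhere: randomised participants divided by calendar months from the opening of recruitment (July 2023) to the last randomisation. Mark it as a clarification made after recruitment began.
2. Reconcile the 1.25 years, the July 2023 to December 2024 calendar, the 3-month wave cadence and the June 2025 finish. If the schedule moved, say so and give both the planned and the actual dates.
3. Keep the pre-determined mark of 9 and restate the full-trial recruitment period as at least 45 months (404/9 = 44.9). Alternatively, keep the 3.5 years and report the observed rate against the required 9.3 to 9.6 per month alongside the criterion of 9.
4. State whether the 3.5 years is recruitment time only, and whether the base is 352 or 364, so that the required rate is a single figure.

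The cost is a few sentences in the outcome, sample size and analysis sections, with no change to conduct. The downside is that, on the current calendar, the recruitment criterion may have to be reported as missed.

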## Discussion

This protocol summarizes a feasibility study of a 6-month virtual, factorial trial of exercise and nutrition among individuals with SCD. This study will inform the suitability of a full-scale trial. Results will also be useful to inform exercise and lifestyle interventions in research and practice, giving insights into feasibility and reach by geography and demographics. Although the frequency of virtual exercise and lifestyle trials increased during the COVID-19 pandemic, few trials recruited broadly from the community as opposed to from established research databases and participant pools. This study will give insights into the feasibility of more generalizable recruitment tactics.

The entirely virtual design will allow recruitment from a large geographic area, including individuals who rarely have access to clinical trials due to geographic region or transportation. The uptake of technology and virtual software (e.g., Zoom®) has accelerated during and after the COVID-19 pandemic [35, 85, 86], enabling reach of interventions to people with few local resources. The feasibility results of this study will inform both a future trial and broader research and practice initiatives.

The trial interventions are grounded in best evidence and practice. The interventions were informed by researchers and practitioners (exercise physiologists, kinesiologists, dietitians, occupational therapists) with subject-matter and practice expertise in exercise, diet, and goal-training. The EX intervention aligns with protocols and guidelines for physical activity for brain health [16, 87]. The DIET intervention is grounded in the “Brain Health Food Guide” recommendations, which is based on single nutrients and overall dietary patterns associated with brain health [26, 55–58]. Furthermore, the DIET intervention exceeds the intensity of prior diet interventions for brain health by combining dietary education with goal setting that has shown to be feasible and effective in other clinical trials, including a pilot study by the research team [51]. Lastly, the inclusion of active control groups that closely equate intervention intensity in terms of time and social interactions, controlling for intervention elements outside of exercise, healthy eating, and goal-training, is another strength. Overall, the use of active controls will result in a conservative estimate of the intervention effect.

However, there are challenges associated with this trial. All assessments will be completed virtually, which is not the gold standard for cognitive tests or fitness assessments. Subjective participation scores measuring adherence may also be biased. Inevitably, technology difficulties will arise, which could impact participants’ adherence and satisfaction, as well as data collection. Furthermore, it is possible that individuals who are uncomfortable with technology and those with lower levels of technology proficiency may be less inclined to join the study despite tablets and/or internet access being provided. As a result, there is a potential for selection bias and the findings not being generalizable to the older adult population.

In conclusion, the results of this study will inform whether it is feasible to move forward with a definitive trial, while also informing future virtual programs and services. If the interventions are feasible and beneficial, this study model could scale up and spread quickly to reach at-risk individuals for the purpose of dementia risk reduction.

